## Abstract

**Background:**

Half of child-welfare-involved children and adolescents meet the criteria for at least one mental health diagnosis. This project proposes to improve successful mental health service linkage in child welfare services (CWS) by adapting and testing the after-action review (AAR) team effectiveness intervention to augment the child and family team (CFT) services’ intervention. Despite being both required and a collaborative approach to service planning, CFT meetings are implemented with questionable fidelity and consistency, rarely including the voice of children and families as intended.

**Methods:**

Using a parallel group trial design, with non-equivalent comparison groups, and qualitative and quantitative methodology, this study will tailor and assess the impact of the AAR on enhancing CFT outcomes. The authors will conduct a qualitative needs assessment targeting the ongoing implementation of the CFT services intervention in a large, publicly funded, CWS system. A qualitative inquiry consisting of interviews and focus groups with key stakeholders will result in the preparation of an action plan to address identified gaps between the current and desired CFT services intervention outcomes. The AAR implementation strategy will be adapted and tailored to address the CFT services’ intervention needs. To test the effectiveness of the AAR on improving outcomes associated with the CFT services intervention, we will utilize blocked randomization of four CWS caseworkers from two CWS system regions to either the intervention condition (CFT + AAR) or standard implementation (CFT as usual). The authors will collect data from the CWS caseworkers and additional CFT members via web-based surveys. Mechanisms of the AAR team effectiveness intervention for CFT implementation will be assessed.

**Discussion:**

By inclusion of child and family voice, the AAR-enhanced CFT should lead to increased fidelity to the CFT intervention and greater levels of parental satisfaction with the service and shared decision-making, thus resulting in enhanced follow-through with service plans and linkage to mental health treatment services for children. The knowledge gained by this randomized clinical trial has the potential to benefit service delivery and integration for CWS leaders, caseworkers, formal and informal CFT member support persons, parents/caregivers, and children with open cases. Improving intervention effectiveness, both at the system and family levels, is crucial for practice efficiencies and improved child and family outcomes.

**Trial registration:**

NCT05629013. Approval date: November 28, 2022 (version 1).

**Trial sponsor:**

University of California, San Diego.

**Responsible party:**

[name].

Contributions to the literature
Limited research in child welfare services (CWS) has focused on the team unit for facilitating successful and sustained child/family engagement in decision-making.Merges the fields of team effectiveness research and implementation science to enhance the child and family team (CFT) services’ intervention with an evidence-based team development intervention.Partnership between two key public sector service settings, CWS and specialty mental health, will facilitate an examination of whether the enhanced CFT meetings result in improved service linkage for children with mental health service needs.

## Child mental health in child welfare

Nearly 620,000 children and youth were victims of child abuse and neglect in 2018 [1]. The burden of child maltreatment includes negative social, emotional, behavioral, and health effects on child victims [2], as well as a fiscal impact. Recent estimates suggest the cost of child maltreatment in the USA, the majority of which results from confirmed cases of child neglect [1], exceeds $400 billion per year [3], a figure which excludes the costs of child welfare services (CWS) unsubstantiated investigations. The prevalence of mental health need is high among child welfare-involved children [4, 5]. Half of child-welfare-involved children and adolescents meet the criteria for at least one current mental disorder [6], the most common of which are disruptive disorder (27%) including conduct disorder (20%) and oppositional defiant disorder (12%), attention-deficit/hyperactivity disorder (11%), anxiety and depressive disorders (18% and 11%, respectively), and posttraumatic stress disorder (4%). Former foster youth report higher rates of mental health concerns and over one third of foster youth with need received no behavioral health services in the prior 12 months [7].

Child-welfare-involved children’s elevated rates of childhood trauma are directly associated with poor mental health and disrupted social development [8]. Evidence increasingly demonstrates the acute and long-term impact of adverse childhood experiences on child mental health, most recently showing the specific child maltreatment impacts in early adolescence, with higher depressive symptoms, trauma symptoms, anxiety symptoms, and externalizing problems [9].

## Family voice and shared decision-making in child welfare services

Engaging families in shared decision-making promotes safety, permanency, and physical and mental wellbeing of children and families in CWS systems and is central to successful service linkage [10]. Effective family engagement occurs when CWS practitioners actively collaborate and partner with family members throughout their involvement with the CWS system, empowering them in the process [10]. For parents receiving CWS, the timely completion of treatment is part of a specified Action Plan. Services can only be effective when clients fully participate, yet tension between collaboration and compliance in CWS is a challenge to meaningful family engagement.

Involving parents in treatment planning through shared decision-making is vital to child outcomes, with fewer child removals and fewer recurrences [11], thus resulting in decreased risk of child trauma, behavioral concerns, and mental health concerns. Yet, neither parents nor caseworkers perceive that Action Plans are created with mutual influence [12]. In fact, most parents believe they have no voice or input [13]. In further disenfranchisement of families, caseworkers often deprioritize their work with parents, focusing instead on mandated interactions to which they are held accountable (e.g., child visitations, court) [14]. Taken together, social work theory and training pay credence to the critical role of family engagement, voice, and decision-making in service plans, yet, in practice, the inclusion of families’ active voices toward the goal of shared decision-making remains largely absent.

## The promise of child and family team (CFT) meetings

Family meeting models such as child and family team (CFT) meetings in CWS are family-centered and collaborative ways to develop individualized, effective service plans based on mutual agreement [15]. Each child or youth is required to have a CFT meeting within 60 days of entering CWS to identify areas of behavioral, emotional, and/or social needs and complete an initial case Action Plan. Relying on teamwork approaches, CFT meetings intend to give children and families a voice in creating and guiding their Action Plans [16], facilitate shared decision-making, empower families to work with CWS agencies [17, 18], and address organizational need for teams to perform “complex, interdependent, dynamic, and ambiguous tasks [19]”. CFT meetings also promote positive outcomes for children—fewer children enter care, more are placed in residential settings [20], and improvement in youth problem behaviors, child functioning, child impairment, and mental health [16]. Parent engagement in CFT meetings is positively associated with permanency outcomes, including more placement in kinship care, placement stability, shorter stays in out-of-home placement, and increased family reunification.

Effective teamwork, required throughout the process of family meetings to ensure fidelity to the model and successful outcomes [15, 21], brings resources, knowledge, and services into family meetings to develop high-quality planning and implementation, which ultimately results in better outcomes for children and families [22]. Yet, in CWS CFT meetings, the quality of teamwork and proper adherence to the family-centered, collaborative view can be impaired by the inherent challenges of serving multiple needs and viewpoints that vary across team members, as well as the pressures and constraints of CWS.

## Shared mental models as a key tenet for team performance

One of the most fundamental challenges in the CFT meeting is parent active participation in shared decision-making, leading to coordinated Action Plans [14, 23]. For example, caseworkers often deprioritize parents’ voice and/or parents are unaware of their intended leadership role in CFT meetings [12, 13]. Because teamwork is not often optimized [15], CFT meetings may be less likely to adhere to the model and be ineffective in engaging parents and reaching a mutually agreed upon Action Plan, including mental health services utilization. One way to better optimize teamwork is to enhance the shared mental models of CFT members. Shared mental model theory posits that effective team performance on tasks requires members to have similar cognitive representations of task requirements, procedures, and members’ responsibilities [24, 25]. Strategies that generate clear shared mental models help team members create a more accurate shared view of a task by teaching each member about the roles and responsibilities of other team members [26]. Strategies that build similar [27], accurate, and shared mental models [28] could clarify and bolster parents’ role in the CFT meeting process.

## After-action reviews as a team implementation strategy

One strategy to enhance shared mental models that improve team performance is the after-action review (AAR). The AAR is an output-focused, team development intervention [29] used for improvement through individual and team-level reflection and learning. While other output-focused team development interventions exist, the AAR holds tremendous promise in enhancing CFT meetings as a team-based implementation strategy.

The goal of AARs is to have team members engage in an activity of reflection following the conclusion of a performance cycle or event [30]. AARs are considered a learning-based intervention since they focus on reflection of the outcome of a work period, and also the processes involved with reaching that outcome [29]. AARs are also optimal following a critical period of performance (such as the CFT meeting). Although originating in the US military to create “a state of mind where everybody is continuously assessing themselves, their units, and their organizations and asking how they can improve” [31], AARs have since been used across a variety of settings [30, 32, 33] to provide a forum for teams to learn, create, and implement plans to improve team interaction that can be applied to future scenarios and goals [32].

AARs allow team members to engage in collective sense-making after an event, overtly reflecting upon the processes and emergent states (e.g., shared mental models) experienced and associated outcomes, and developing strategies and goals for future events to improve upon future outcomes [30]. For example, AARs facilitate team performance via the emergent state of enhanced psychological safety [30, 34], an integral mechanism in which mutual respect and an atmosphere that is blame-free enable participants to feel safe sharing and discussing [35] and improved team processes, such as communication and coordination. When individual views are shared in a well-facilitated discussion, these perspectives can be supported, challenged, modified, and combined until some degree of consensus between team members is achieved [30]. By targeting team processes and emergent states, teams that employ AARs can improve their effectiveness by 25% [36], with downstream impacts to improved patient outcomes across medical settings [37, 38].

## Mechanistic model and how AARs will improve child/parent outcomes

This project aims to leverage and apply knowledge from the field of team effectiveness research to improve CWS child/family outcomes. Specifically, the proposed project will enhance the current CFT services intervention with an evidence-based team development intervention (i.e., AARs) to improve the mechanisms of team processes and team emergent states for CFT members (including CWS caseworkers and children/families), resulting in enhanced service/clinical outcomes (i.e., specialty mental health services linkage).

The AAR team development intervention, hereafter referred to as CFT + AAR, is hypothesized to improve outcomes associated with the CFT meeting services intervention through enhanced team processes and emergent states. See Fig. 1 for the proposed mechanistic model and Table 1 for the proposed measures for model constructs. The AAR aims to boost emergent states of stronger shared mental models amongst team members (Cognition), and greater levels of trust and psychological safety amongst team members (Affect). Additionally, the AAR intends to improve team processes of communication and coordination (Actions) and positive perceptions of the specified goal and formulated strategy for the CWS child/family Action Plan (Transition). By enhancing the mechanisms of emergent states and team processes, the AAR facilitates improved fidelity and child/family outcomes. Specifically, CFT meeting fidelity is exemplified when child/family voice and shared decision-making amongst team members is present. When CFT meeting fidelity is enhanced, greater satisfaction with the child/family Action Plan may be achieved, ultimately resulting in successful specialty mental health services linkage.

**Fig. 1 Fig1:**
[figure not shown]
Mechanistic model to adapt and apply the after-action review to implementation of child and family team meetings

**Table 1 Tab1:** Measures for model constructs by intervention group

Measure	Construct	CFT	CFT + AAR
**Input**			
Demographics	Team member characteristics	✓	✓
**Mechanisms**			
Working Alliance Inventory-Short Revised (WAI-SR) Goal	Team Processes Goal Specification	✓	✓
Working Alliance Inventory-Short Revised (WAI-SR) Task	Team Processes Strategy Formulation	✓	✓
Collaboration & Satisfaction About Care Decisions (CSACD)—Collaboration	Team Processes Communication and Coordination	✓	✓
Working Alliance Inventory-Short Revised (WAI-SR) Bond	Emergent States Trust	✓	✓
Card-Sorting Task	Emergent States Shared Mental Model	✓	✓
McAllister Affect-Based Trust	Emergent States Trust	✓	✓
Psychological Safety Climate Measure	Emergent States Psychological Safety	✓	✓
**Outcomes**			
Feasibility of Intervention Measure (FIM)	AAR Team Implementation Strategy Feasibility		✓
Acceptability of Intervention Measure (AIM)	AAR Team Implementation Strategy Acceptability		✓
Intervention Appropriateness Measure (IAM)	AAR Team Implementation Strategy Appropriateness		✓
Working Alliance Inventory-Short Revised (WAI-SR) Overall Score	CFT Clinical Intervention Fidelity Overall collaborative relationship	✓	✓
Parent Participation Engagement Measure (PPEM)	CFT Clinical Intervention Fidelity Collaboration and engagement	✓	✓
Collaboration & Satisfaction About Care Decisions (CSACD)—Satisfaction	CFT Clinical Intervention Outcome Satisfaction with decisions	✓	✓
SD County Behavioral Health Administrative Data	CFT Clinical Intervention Outcome Behavioral Health Service Linkage	✓	✓

Within team environments, shared mental models refer to the degree to which individual team members perceive key concepts (i.e., team, task) in a similar manner. For the CFT services intervention, shared mental models regarding perceptions of member roles, responsibilities, and goals can mediate more effective and efficient treatment planning. Team affect (i.e., trust and psychological safety) may also serve as mechanisms mediating success of the CFT services intervention. Psychological safety, a group-level phenomenon that correlates with team learning behaviors and performance, facilitates team members’ feelings of security [39] and focus on collective goals and problem prevention, rather than on self-protection [40–44]. Similarly, team trust is associated with decreased inefficiencies, greater negotiating effectiveness, and greater team effort, thus mediating overall team effectiveness [45–47]. Given the sensitivity and high stakes associated with CFT meetings (i.e., child placement, reunification), CFT members—particularly children/family—may feel uncomfortable fully participating for fear of negative repercussions. When CFT members experience enhanced shared mental models, psychological safety, and trust, they may be more open and willing to voice their opinions to collaborate on the treatment planning process for the CWS case.

The AAR also aims to result in high-quality team processes exemplified by greater communication and coordination (Actions), and more positive perceptions of the specified goal and formulated strategy for the CWS child/family case (Transition). Group psychological safety and trust can influence “speaking up, or voice” [48], or verbal communication among team members. This open communication is vital for the CFT services intervention to reach its desired outcome—shared decision-making among team members, including CWS children/families, with regard to goals and the Action Plan. By targeting these proximal team effects, the AAR team-based implementation strategy aims to enhance CFT services intervention through the inclusion of child/family voice and shared decision-making. By increasing fidelity to the CFT services intervention, CWS child and family members may exhibit greater levels of satisfaction with the Action Plan, and specifically improved linkage to needed specialty behavioral health services.

## Method

This study is part of a National Institute of Mental Health Advanced Laboratories for Accelerating the Reach and Impact of Treatments for Youth and Adults with Mental Illness Center [Center is P50 MH126231-01A1] that will implement a randomized control trial to develop and test team-based implementation strategies to improve services for children with mental health and developmental needs across service systems. This study aims to leverage and apply knowledge from team effectiveness research to improve outcomes associated with the services intervention currently used in CWS CFTs. Guided by the Exploration, Preparation, Implementation, Sustainment (EPIS) framework [49] and the Center’s Team Effectiveness for Implementation Science model (Fig. 1), this study aims to adapt and apply the team development intervention of the AAR to the implementation of the CFT meeting for a large, publicly funded, CWS system. Using a parallel group trial design, with non-equivalent comparison groups, and qualitative and quantitative methodology, this study will tailor and assess the impact of the AAR on enhancing CFT outcomes.

### Study objectives

#### Specific aim 1

Consistent with EPIS Exploration and Preparation phases, the research team will use qualitative methodology to explore current CFT clinical intervention implementation efforts in a large, publicly funded, county CWS system to better understand discrepancies that may exist between current and desired CFT services intervention outcomes. The needs assessment will occur over three phases.

Working in collaboration with County CWS, the first phase will center on defining the focus and scope of the needs assessment. Specifically, areas of concern regarding current CFT services’ intervention implementation efforts will be uncovered through informant interviews and focus groups with key stakeholders, including CWS leadership, supervisors, and front-line providers, as well as CWS-involved caregivers. Need indicators and/or data that have potential to confirm revealed concerns will be identified. Data sources to address and explore the magnitude of the uncovered concerns will be considered and prioritized.

The second phase will center on gathering and analysis of data. Specifically, this second phase will document the current status of CFT services’ intervention implementation efforts with regard to the concerns identified in phase one, including identification of mental health services linkage for children. Results from the data collected will be compared to the desired CFT services intervention outcomes. A list of need areas, wherein a discrepancy exists between current and desired CFT services intervention outcomes, will be compiled and factors that may be amenable to intervention will be identified.

The third phase of the need assessment aims to facilitate the preparation of an action plan to address the needs. The list of needs from phase two will be prioritized based on the magnitude of the discrepancy between current and desired outcomes, degree of difficulty in addressing the needs, and the potential consequences of neglecting the needs. Possible solutions to address the prioritized needs will be generated and examined. An action plan linking the needs with solutions will be prepared.

Interview and focus group data will be analyzed iteratively using a template organizing style [50]. Recordings will be professionally transcribed, checked for accuracy, and imported into NVivo software [51]. Transcripts will be read to gain familiarity with the content and to identify themes. NVivo will be used for line-by-line coding [52] using an a priori code list that was developed from theoretical and conceptual considerations and the initial reading of the transcripts. While the coding scheme will be formed along predetermined categories, it will remain flexible to accommodate new codes. Analytic processes will be reviewed by the Methods Core qualitative methods team.

#### Specific aim 2

Consistent with the EPIS Preparation phase, the research team will use the prepared action plan (Specific Aim 1) to generate an adapted and tailored AAR implementation strategy to address CFT services intervention needs. A collaborative process between the research team and CWS leadership resulted in the selection of the AAR as the team-based implementation strategy most appropriate for improving the CFT in CWS based upon its real-time applicability, the complexity of the “team”, and all team members being in a shared space.

Adaptations for the AAR will ensure maintenance to the core four questions AARs aim to answer [53]: (1) What was expected to happen?; (2) What actually occurred?; (3) What went well, and why?; and (4) What can be improved, and how? First, a general AAR tool based upon factors shown to be important for team effectiveness [54] that incorporates the twelve evidence-based practices for effective AARs [32] will be developed. The AAR tool will be further tailored and adapted to incorporate the needs prioritized through Specific aim 1. An iterative process with CWS stakeholders (Specific aim 1) will review the adapted AAR tool until consensus on its applicability is reached.

#### Specific aim 3—interventions and comparisons

Consistent with the EPIS Implementation phase, the research team will pilot-test the AAR implementation strategy on improving CFT outcomes and explore team mechanisms. Specifically, to test the effectiveness of the AAR on improving outcomes associated with the CFT services intervention, we will implement randomization with parallel assignment in two CWS system regions, at the caseworker level. In each region, four CWS caseworkers will be followed as they engage in 5 CFT meetings (8 CWS caseworkers total). Within each region, two of the CWS caseworkers will be assigned to the team-enhanced implementation strategy, CFT + AAR (4 CWS caseworkers total), and two CWS caseworkers will be assigned to the standard implementation, CFT as usual (4 CWS caseworkers total). CFT as usual consists of CFT Meeting Facilitation wherein a mental health services organization partners with CWS to schedule the CFT meetings. The research team will utilize blocked randomization of CWS caseworker to intervention condition (CFT + AAR or CFT as usual) to ensure equal group sizes. As such, assignment of condition will be implemented by the research team without concealment or blinding.

Child mental health concerns are identified by a preliminary administration of the Child & Adolescent Needs & Strengths (CANS) [55] assessment for children aged 6–17 by the CWS caseworker at the initial family visit, which typically occurs 2–3 weeks prior to the initial CFT meeting. Based upon this initial visit and preliminary CANS results, informal and formal support persons are invited to the CFT meeting by the CFT Meeting Facilitation program. The CANS results are an integral component of the initial CFT meeting, during which the CWS caseworker guides discussion around the mental health needs that emerged from the initial CANS assessment and finalizes the Action Plan to attend to these needs. In addition to the above, those in the CFT + AAR will be guided through the AAR team effectiveness intervention, as facilitated by research staff, immediately following the CFT meeting. To optimize assessment of mental health services linkage, only CFTs which include a child with an identified mental health service determined by the preliminary administration of the CANS assessment by the CWS caseworker at the initial family visit will be included.

Immediately upon completion of each of the 5 CFT or CFT + AAR team meetings, the CWS caseworkers together with ~ 7 additional CFT members will provide data a via web-based online survey to assess mechanisms and outcomes. This results in 8 caseworkers leading 5 CFTs each for a total of 40 unique CFTs. Each of the 40 CFTs has ~8 participants, for a minimum total of 320 data points. See Fig. 2 for sampling.

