### Participants

There are four types of participants in this study. Participants will be (1) County CWS system leaders and caseworkers, (2) CFT informal and formal meeting members, (3) parents/caregivers with open CWS cases, and (4) children aged 6–17 with open CWS case. CWS caseworkers and CFT informal and formal support persons will be ≥ 18 years of age. Children and family members urrently open to CWS have a minimum age eligibility of 6 years to correspond with the CWS protocol for screening for behavioral health services need, and no maximum age limit for eligibility. Participants will be recruited from select regions, which will be determined in collaboration with CWS leadership prior to project implementation. Inclusion criteria for all groups of participants are intentionally broad to ensure valid analyses.

The research team will partner with County CWS to identify appropriate and representative CWS caseworkers to follow over the course of 5 CFT meetings. The 5 CFT meetings per CWS caseworker will be identified to best represent County CWS open cases. Additionally, only CFTs which include a child with an identified behavioral health services need will be included to optimize assessment of behavioral health services linkage. Behavioral health service need is determined by a preliminary administration of the Child & Adolescent Needs and Strengths (CANS) assessment by the CWS caseworker at the initial family visit. The CANS behavioral and emotional needs domain is employed for all children aged 6–17 as the screener for behavioral health services.

For children aged 6–17 open to CWS and with mental health services needs (identified via CANS screening and confirmed during initial CFT meeting perusual CWS), County Behavioral Health administrative data will be extracted to determine mental health service linkage. While children aged 6–17 may also participate in the CFT meeting, this is considered part of usual CWS services. No additional study participation from these children will be solicited. The proposed study will not apply any gender or minority exclusion criteria for participant selection. All efforts will be made to ensure that women and minority representation will be representative of County CWS.

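### Caseworkers are assigned openly by the team that helps choose them, though blocking for equal group sizes does not require giving up concealment; with four caseworkers per arm, steered placement could make the arms differ before any AAR

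*Protocol article*

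**What the plan says.** Specific aim 3 fixes the numbers: "In each region, four CWS caseworkers will be followed as they engage in 5 CFT meetings (8 CWS caseworkers total"). Each region's four are split evenly, two to CFT + AAR and two to CFT as usual, which makes four per arm. On method it says: "The research team will utilize blocked randomization of CWS caseworker to intervention condition (CFT + AAR or CFT as usual) to ensure equal group sizes". The next sentence draws a consequence from that: "As such, assignment of condition will be implemented by the research team without concealment or blinding". The same section has research staff facilitate the AAR.

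On who enters the trial, the Participants section says: "The research team will partner with County CWS to identify appropriate and representative CWS caseworkers to follow over the course of 5 CFT meetings".

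The opening of the Method section describes the study as follows: "Using a parallel group trial design, with non-equivalent comparison groups, and qualitative and quantitative methodology". The Methods part of the Abstract uses the same description. Yet the Discussion part of the Abstract and the Method section both call the study randomised, and Specific aim 3 randomises caseworkers.

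**The concern.** Two things are run together in one sentence. Caseworkers and AAR facilitators can hardly be blinded once the condition is known. Concealing the assignment until the caseworkers are settled is a different matter, and it is feasible here. The article gives up both and offers blocking as the reason. Blocking fixes how many caseworkers go to each arm; it does not decide who may see the list or when.

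The consequence is that one team takes part in choosing the units by judgement, assigns them openly and delivers the intervention. Two routes to steering follow. With an open list, a given caseworker can be matched to a given slot. With one-by-one selection from a wider pool, the choice of the next caseworker can depend on the arm that is coming.

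What is at stake is comparability at the only level that is randomised. If caseworkers who already run more collaborative meetings end up in CFT + AAR, member-rated alliance, trust, safety and satisfaction could favour that arm without any AAR effect. The survey measures are described only after each meeting, so there is no earlier reading to reveal or adjust for such a difference.

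The label of non-equivalent groups adds to the uncertainty. It normally belongs to a non-randomised design and leaves the reader unsure which kind of comparison is claimed.

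**Working it through.** **Inputs.** Two regions, four caseworkers each, split 2:2, five CFT meetings per caseworker (Specific aim 3); about eight respondents per meeting, 320 assessments in all (Specific aim 3, Fig. 2 note). ρ = 0.20, effective sample size 36 and f² = 0.10 (Power analysis). The block size is not stated in words; a block of four is inferred from two and two among four.

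**1. The stated allocation reproduces.** 2 × 4 = 8 caseworkers; 2 × 2 = 4 per arm.

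**2. Weight of one caseworker.** 5 × 8 = 40 ratings each. An arm has 4 × 5 = 20 meetings and 4 × 40 = 160 ratings, so one caseworker is 5/20 = 40/160 = 25% of an arm.

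**3. What can be foreseen by counting places left.** There are C(4,2) = 6 orderings of a 2:2 block. With one-after-another entry, a guesser who names the arm with more places left is right with probability 1/2, 2/3, 2/3 and 1 at the four positions: (0.50 + 0.67 + 0.67 + 1.00)/4 = 0.708. The fourth place is always known, and the third is known when the first two match (2 of 6 orderings): 1 + 1/3 = 1.33 of 4 per region, 2.67 of 8 overall. Blocks of two would give 75% correct guesses and 4 of 8 known. If the list itself is open, all 8 are known.

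**4. When foreseeing does and does not bias.** Suppose the four names in a region are already fixed, the sequence is random, and the team sees only past assignments. Whatever rule it uses to order the four, each of the six possible splits is reached by exactly one of the six equally likely sequences. Every split keeps probability 1/6, and no bias arises from step 3. Bias needs one of two further conditions: the coming assignments can be read from an open list, or the next caseworker is picked from a wider pool after earlier assignments are seen. The article excludes neither. It does not say whether entry is simultaneous or sequential, and it describes no independent holder of the sequence.

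**5. Size, over an assumed range.** The caseworker share of total variance is not given. The Power analysis describes ρ = 0.20 as nesting of members within meetings. Its 36 reproduces only with clusters of 40, one caseworker's ratings: 320/(1 + 39 × 0.20) = 320/8.8 = 36.4 (clusters of 8 would give 320/2.4 = 133). So 0.20 is used here as the top of an assumed range, not as a stated caseworker figure. Let s = √share be the caseworker SD in units of the total SD. Choosing one caseworker one s better for an arm moves that arm's mean, and hence the difference, by s/4. Swapping a pair one s apart between arms moves the difference by 2 × s/4 = s/2.

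| Assumed share | s | One chosen, s/4 | One pair swapped, s/2 |
|---|---|---|---|
| 0.02 | 0.14 | 0.04 SD | 0.07 SD |
| 0.05 | 0.22 | 0.06 SD | 0.11 SD |
| 0.20 | 0.45 | 0.11 SD | 0.22 SD |

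For scale, f² = 0.10 corresponds to a standardised difference of 2√0.10 = 0.63, so one swap is 11% to 35% of it. That benchmark is itself doubtful: with 36 independent observations, 80% power needs f² of about 0.23, a difference of 2√0.23 = 0.96, and one swap is then 7% to 23%.

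**The case against.** The best defence is that Specific aim 3 does promise randomisation, that selection is shared with County CWS and aims at representative staff, and that nothing in the article shows steering or imbalance. All of that stands. If the four caseworkers in a region are named first and then assigned together by an honest draw, little is left of the concern beyond the wording. The article does not commit to that order, however, and its own sentence rules out concealment.

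Two stronger readings are tempting. A reader might infer that 71% predictability in itself biases the arms. Step 4 shows that it does not when the names are fixed. A reader might also model the team as always placing the two caseworkers judged better in CFT + AAR. In simulations with no AAR effect and a caseworker share of 0.20, that gives spurious differences of 0.18, 0.30 and 0.59 SD, and false-positive rates of 7%, 12% and 52% for a caseworker-level t test, when the judgement correlates 0.3, 0.5 and 1 with true quality. Those figures describe full deliberate placement with no randomisation, which the article does not plan. They also hang on the assumed share: at a correlation of 0.5, shares of 0.05 and 0.02 give 0.15 and 0.09 SD, with rejection rates of 10% and 8%. They should not be cited as the expected effect of this design.

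Aim 3 is also called a pilot test. That tempers the weight of the point but does not remove it, because the same section sets out to test effectiveness and the Power analysis is built around that test.

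**Conclusion.** The point holds as an avoidable, stated weakness in the assignment procedure. Blocking does not justify open assignment, and the team that assigns also helps choose the caseworkers and facilitates the AAR. With four caseworkers per arm, a single steered placement carries weight: 0.04 to 0.11 SD for one chosen caseworker and 0.07 to 0.22 SD for one swapped pair, under assumed caseworker shares of 0.02 to 0.20 and caseworkers one caseworker-SD apart. The surveys described give no earlier measure with which the analysis could remove such a shift.

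The conclusion rests on the list being open or on caseworkers being picked in turn from a wider pool; the article leaves both possible. It does not establish that the arms differ or that anyone intends to steer them. Nor is the lack of blinding of caseworkers and facilitators part of the fault. The non-equivalent label is a wording contradiction that the same edit can settle.

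**What to change.** In Specific aim 3, replace the sentence on concealment and blinding with:

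> All four caseworkers in each region will be identified, and their agreement recorded, before any assignment. One of the six possible 2:2 allocations per region will then be drawn by computer for all four at once, by a person with no part in choosing caseworkers or facilitating the AAR, and released only after the list of names is locked. Caseworkers and AAR facilitators cannot be blinded after assignment.

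The last sentence is limited to those two groups on purpose: service linkage comes from County administrative data, and the article gives no reason why its extraction could not be blinded.

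In the Abstract (Methods) and the opening of the Method section, replace the words on non-equivalent comparison groups with *caseworkers randomised within region*.

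After the change there are 6 equally likely splits per region (6 × 6 = 36 over both), no assignment is known before the names are locked, and the arms stay at four and four. The change needs no extra participants; it takes one computer draw per region by someone outside selection and facilitation. The small downside is that all four caseworkers in a region must be named before the first one starts.
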